### Group 2 - intervention group

KTRs allocated to the intervention arm will receive identical routine post-transplant aftercare as the patients in the control group (see above, **Table 1**). In addition, they will receive predefined interventional telemedical management by a separate telemedicine team as outlined above. Participants in the telemedicine group will have a certified app (comjoodoc EASY run by Carealytix Digital Health GmbH, Valley, Germany) that allows automatic data transfer (e.g., vital signs, wellbeing, medication plan, laboratory data, and chat) via a smartphone or tablet between the patient and a KTC (54). To increase the comfort of self-monitoring and easy documentation, the patients will be offered devices that directly transfer data into the smartphone app via standard Bluetooth connectivity. Moreover, participants in the intervention group will receive urine dipsticks with appropriate education to support early diagnosis of urinary tract infections at home. Finally, the patients will receive extensive education on medical therapy, counseling on adherence, and information on telemedicine management. Home nephrologists willing to participate and equipped with appropriate software (e.g., Nephro7 by MedVision AG, Unna, Germany) may participate in automatic data exchange of key variables (such as vital signs and laboratory data) with the KTC.

### Inclusion criteria

Kidney transplantation within the last 12 monthsTreatment with tacrolimusRoutine aftercare planned at a KTCAbility to use a smartphone or tablet, or with the help of someone close byFor children < 12 years, parents have to take over the use of the smartphonePatients who are willing and able to participate in the study and from whom written informed consent has been obtained prior to study participation or pediatric patients with parental consentAbility to communicate in German or EnglishAdequate and stable renal function (eGFR > 30 ml/min, proteinuria < 1g/g creatinine if not pre-existing before KTx); eGFR will be determined according to CKD-EPI for adults or Schwartz formula for children

### Exclusion criteria

Patients with mental dysfunction or inability to comply with the study protocol or pediatric patients whose parents cannot comply with the study protocolAny significant diseases or clinically significant findings, including psychiatric and behavioral problems, medical history, and/or physical examination findings that would, in the opinion of the investigator, preclude the patient from participating in the studyHistory of alcohol or drug abuse with less than 6 months of sobrietyParticipation in any other interventional clinical trial less than 1 month before participation in this studyPatients who have been institutionalized by official or court orderPatients with a combined kidney transplant or multi-organ recipients [other solid organ (e.g., pancreas) or bone marrow]Presence of DSA with MFI > 1,000 at time of transplantationRecurrence of underlying kidney disease [e.g., focal segmental glomerulosclerosis (FSGS) or atypical hemolytic uremic syndrome (aHUS)]Patients with active malignancy post-transplant with the exception of local, non-invasive, fully excised, cutaneous basal cell carcinoma, cutaneous squamous cell carcinoma, or cervical carcinoma *in situ*
Patients with clinically symptomatic congestive heart failure (CHF) or symptomatic coronary artery diseasePatients with documented [either by serology and/or nucleic acid testing (NAT)] clinically active infections [e.g., with a known hepatitis B (HBV), hepatitis C (HCV), HIV, CMV, or BK virus infection]

### Telemedicine team

A separate telemedicine team will constantly review the incoming data according to a predefined protocol, as outlined in **Tables 2**, **3**, and eventually contact the patient and/or the home nephrologist to start appropriate interventions. The team consists of experienced nurses/case managers together with physicians in the KTC. For patients in the intervention arm, physicians will use the certified iBox algorithm (Predict4Health, Paris, France) to better detect patients at risk for early graft failure. Physicians and the telemedicine teams will also use certified software (ID Medics ^®^, ID GmbH & Co. KGaA, Berlin, Germany) to check drug-drug interactions easily.

**Table 2 T2:** Treatment ranges of vital signs and wellbeing in adults.

Characteristic	Critical	Suspicious	Normal	Suspicious	Critical
Systolic blood pressure [mmHg]	<90	<100	100 – 129	130 – 180	>180
Diastolic blood pressure [mmHg]	<50	50 – 59	60 – 89	90 – 100	>100
Heart rate [bpm]	<50	50 – 59	60 – 89	90 – 120	>120
Temperature [°C]	<33.5	33,5 –3 6,2	36,3 – 37,4	37.5 – 38,0	>38.0
Weight change, 1 day [kg]	>(–1,5)	(-1,5) – (-0,5)	+/-0.5	0.5 – 1.5	>1,5
3 days [kg]	>(-2,5)	(-2,5) – (-1,0)	+/-1.0kg	1.0 – 2.5	>2.5
8 days [kg]	>(-3.0)	(-3,0) – (-1,5)		1.5 – 3.0	>3.0
Wellbeing [points]			1 – 2	3 – 4	5

**Table 3 T3:** Telemedicine aftercare tasks.

Prioritization	Nurse	Physician	Senior nephrologists	Local nephrologists
1.	Reports critical vital signs to the physician	Contacts patients with critical values	Guides critical cases	Receives data from the transplant center
2.	Informs the physician on duty	Discusses critical cases with the transplant team’s senior nephrologist	Support for clinical questions	Reviews incoming data
3.	Reports critical values to the physician	Takes action if needed (e.g., contacts local nephrologist or emergency room)	Reviews problematic cases	Performs the onboarding process for new patients
4.	Reviews wellbeing	Reviews problematic cases with the telemedicine nurse	Contact local nephrologists	Can call the telemedicine team in case of technical problems
5.	Calls patients if they are not feeling good	Reviews cases with the transplant team and the senior nephrologist	Reviews critical drug-drug interactions	Can call telemedicine team in the case of medical questions
6.	Discusses critical patients with the physician on duty	Reviews incoming messages and laboratory data	Reviews critical iBox results	May receive calls from telemedicine team regarding problematic patients
7.	Reviews less critical vital signs	Follows problematic cases	Participates in case conferences	Can discuss problematic patients with the telemedicine team, transplant center, or senior nephrologist
8.	Reviews patients with missing data	Answers incoming calls from patients and local nephrologists		May receive re- training
9.	Calls patients who did not transfer data according to the schedule	Trains and re-trains local nephrologists and patients		May participate in case conferences
10.	Discusses problematic cases with the physician on duty	Reviews drug-drug interactions reviews iBox scores		
11.	Reviews normal vital signs			
12.	Answers incoming calls from patients and local nephrologists			
13.	Reviews incoming medical messages	Onboarding of patients		
14.		Organizes and participates in case conferences		
15.	Onboarding of patients			
	Participates in case conferences			

### Onboarding procedure and training of participants

After randomization, a detailed training and onboarding process with the patient will be performed [65], including the following: the app solution is installed on a smartphone and the patient receives instructions from the telemedicine team on how to use the app and how to document vital signs and medication changes. Patients are offered certified devices (scale, blood pressure monitor, and thermometer), which optionally allow them to directly transfer data to a tested and secure mobile software application via Bluetooth connection to increase the ease of self-monitoring. Participants receive urine dipsticks along with appropriate instructions for when to use and how to react in case of symptoms of urinary tract infection. The medication plan is reviewed in the app to ensure correct transmission. The patient will receive instructions on how to document drug intake. With the help of the telemedicine team, the use of the mobile chat messenger and the video system is tested and participants will be instructed to contact the telemedicine team in case of medical or technical questions. Patients will be instructed on the availability of the telemedicine team during regular working hours only and how to handle emergency situations.

### Daily monitoring of incoming data

The patient will document their vital signs, wellbeing, and drug intake in the mobile software application. Data will then be transferred to the telemedicine team in the KTC (54), who will review all incoming data from 8 am to 4 pm on weekdays in a structured way as described in **Table 2**, according to predefined thresholds (54) as outlined in **Table 4**. If the values are outside the critical range, the telemedicine team will contact the patient to clarify the situation and take appropriate action. As outlined in **Table 2**, the telemedicine team may also discuss the medical issue with the KTC or home nephrologist. In the case of a medical emergency or critical data, the telemedicine team will organize appropriate and fast medical help in an emergency unit, eventually with the help of the KTC or home nephrologist.

**Table 4 T4:** Description of the telemedicine service.

Telemedicine services, app	Telemedicine team
Any time	8 am – 4 pm on working days
Transmission and documentation of vital signs, wellbeing, blood sugar (for diabetic patients), and daily steps	Review of vital signs, laboratory values, and wellbeing on working days
Display of medication plan	Review of medication changes
Display of laboratory values	Medical hotline
Tracking of medication intake	Review of adherence
Reminder of medication intake	Recognition of non-adherence
Messages to transplant center	Intervention and individualized lessons
Video consultations with transplant center	Phone calls and medical messages (questions, problems, assistance, receipts, appointments, etc.)
	Semi-structured onboarding of patients (incl. technical aspects, education, self-assessment, important symptoms, medication plan, and handling of medical emergencies)
	Review of drug-drug interactions, iBox score
	Technical support for patients and home nephrologists

Acute medical problems and symptoms and emergency care remain unchanged and are provided by physicians on call, home nephrologists, and emergency rooms.

The telemedicine team will also review the patient’s regular drug intake and whether the patient follows the individual therapeutic plan, which was agreed upon during the onboarding procedure. If the patient’s adherence (either to drug intake or therapeutic plan) decreases, the telemedicine team will get in touch with the patient and assess reasons for non-adherence. Eventually, the therapeutic plan will be adjusted to the needs of the patient. Some patients may be educated again on the importance of adherence and how to implement it in their daily lives. If necessary, the telemedicine teams may repeat this educational session and organize a face-to-face meeting or discuss other supportive measures.

### Sharing of laboratory values

Patients in the intervention group will receive the lab results of key data, such as renal function or tacrolimus trough levels, directly in the app to increase awareness and empower the patients. In addition, key laboratory data may be exchanged with the home nephrologists, who are willing to participate and use an appropriate patient documentation system (e.g., Nephro7, MedVision AG, Unna, Germany). This means that more longitudinal data will be available for the treating physician at the KTC and home nephrologist, which may allow more timely detection of critical situations and better coordinated care.

### Case conferences

The telemedicine team will perform regular case conferences on a monthly basis. During these conferences, difficult cases and important results from drug-drug interaction checks or abnormal findings in iBox will be discussed together with the physicians of the KTC and home nephrologists.

### Certified decision support for individual patient risk assessment and allograft survival prediction

The certified iBox^®^ software will be used for allograft survival prediction and assessment of the individual patient risk for graft loss at each study visit. In the case of abnormal results, an internal review with senior physicians will take place to discuss potential interventions and/or close follow-up monitoring.

### Regular assessment of drug-drug interactions

The telemedicine team will use the certified software ID Medics^®^ for participants in the intervention group to assess potentially harmful drug-drug interactions regularly. The current medication plan will be transmitted directly to the patient app. Any medication changes by the KTC will release a new plan, which will again be transferred to the patient directly. Important findings will be discussed with the senior nephrologist in the KTC and during case conferences.

### Randomization

Randomization will be performed using a predefined variable block randomization scheme, stratified by the participating centers and the age of the participant. Due to low expected patient numbers in the age groups of < 12 years and 12 to 18 years, patients in these age groups will be randomly stratified by age, but not by KTC. The randomization scheme will be generated and reviewed by the study biostatistician and quality assurance staff and locked by them after approval. The investigation sites will assign eligible patients through an interactive internet-based computer system (IWRS) once a patient has satisfied the requirements to be included in the study. The IWRS randomization tool is part of the eCRF (Secutrial^®^, interActive Systems, Berlin, Germany). After screening for eligibility and assignment of the individual PID, each patient can only be assigned once to one of the treatment arms. Using the web-based tool will make it impossible for the study personnel to predict the assignment. The sites will record the time of randomization. Treatment in the assigned group starts in the first year after the kidney transplantation and ends in month 12 after randomization.

### Study visits

There are five planned study visits and two additional visits for capturing tacrolimus trough levels during the trial period.

### Baseline visit

At baseline (=visit 1), the patients will undergo routine medical examinations and central randomization will be performed to one of the two treatment groups in a 1:1 ratio. Different questionnaires will be assessed on paper or in electronic form. The established treatment will be continued until month 12, when the last control assessment will be performed. Investigators will be instructed to change immunosuppression only if necessary and based on clinical grounds. For any change in the immunosuppressive regimen, the investigator should explain this in the eCRF.

After the baseline visit, there will be four additional study visits during the 12-month treatment period.

Visit 2: 3 months ± 14 days after baseline

Visit 3: 6 months ± 21 days after baseline

Visit 4: 9 months ± 21 days after baseline

At the visits, 2–4 regular safety assessments (AEs/SAEs and AEs of special interest) and documentation of medication, BPAR, graft loss, and death will take place. The visit plan in section 4.7 shows the items to be evaluated at each time point. The different questionnaires will be assessed on paper or in electronic form. Most importantly, all visits and physician contact at the KTC, with the home nephrologists, the emergency unit, or admission to any hospital will be documented.

### Additional study visits

At two additional time points (at month 7.5 and month 10.5), tacrolimus trough levels will be captured and analyzed at the KTC. If blood is drawn outside the KTC, samples will be shipped to the laboratory to assess the patient’s tacrolimus trough level.

Additional visits in the transplant center may be necessary as per routine practice or for clinical reasons, such as a sign or symptom of drug toxicity/intolerance, an adverse event, or a suspected acute rejection episode, at any time during the study. During these additional visits, risk evaluation (blood, urine, and biopsy) with iBox Score can be performed when deemed necessary by the local investigator according to local policy or in situations such as allograft biopsy, anti-HLA DSA assessment, or deterioration of allograft function (estimated glomerular filtration rate, proteinuria). Furthermore, additional laboratory parameters may be obtained at study visits, if clinically indicated. In general, all patients should be followed according to local practice and as recommended by KDIGO clinical practice guidelines for the care of kidney transplant recipients (65).

### Dose of immunosuppressants and tacrolimus trough level monitoring

The doses of all immunosuppressants being administered to the patient will be recorded on the appropriate eCRF page at each study visit, as will any time a change in dosage is made and at any time a whole blood tacrolimus trough level is measured.

Whole blood, for tacrolimus trough level measurement, will be drawn within 30 minutes before the morning dose of tacrolimus at each study visit. Dose adjustments to maintain tacrolimus whole blood trough levels within the predefined therapeutic range will be based on local laboratory determinations. Each site should submit its local procedures for tacrolimus trough levels before beginning enrolment.

Investigators will be instructed to change immunosuppressant doses only if necessary (e.g., based on clinical grounds or trough levels far outside the target range).

### Study endpoints

The primary endpoint will be measured via seven indicators: BAASIS Score (adherent) after 12 months, IPV of tacrolimus trough levels < 30% between months 6 and 12, number of unplanned hospitalizations in 12 months, number of unplanned hospitalizations > 10 nights in 12 months, normal 24h blood pressure profile at 12 months, no *de novo* DSA at 12 months, and eGFR ≥ 45ml/min at 12 months. Each indicator of the primary endpoint can be defined as achieved (=1) or not achieved (=0) for each patient. The primary endpoint is calculated by an unweighted sum of the achievement of the indicators (min = 0, max = 7). Secondary endpoints were graft failure within 12 months, better iBox prognosis at 12 months, increase in quality of life (self-report) over 12 months, increase in illness management (self-report) over 12 months, and incremental cost-effectiveness. In addition, acceptance of the patients and the telemedicine teams of the new telemedical approach will be measured.

*Adherence* will be determined by the BAASIS questionnaire (38) at month 12. Non-adherence is defined as “yes” to any of the questions. For patients without valid responses to the questionnaire, the response to the BAASIS questionnaire at month 9 will be imputed. Patients who did not respond to the questionnaire at months 9 and 12 will be considered non-adherent.

*Tacrolimus IPV* will be determined from tacrolimus trough levels at months 6, 7.5, 9, 10.5, and 12. To determine tacrolimus trough levels at months 7.5 and 10.5, patients will undergo a blood draw at home (either nephrologist or a general practitioner) or at a KTC according to the patient’s decision. If necessary, whole blood will be shipped by mail to the transplant center for central evaluation. For patients with tacrolimus levels of less than 3 (except for patients with graft loss or switch to another immunosuppressant), high tacrolimus IPV will be assumed.

*Hospitalization* is defined as an unplanned hospital admission resulting in an overnight stay where the length of stay is at least 24 hours. All events leading to an emergency room visit with a stay under 24 hours will not be classified as hospitalization. For a hospitalization that is considered planned, the patient must not have had signs or symptoms of a worsened disease or need for intensified therapy. The date of admission must be arbitrary. Planned hospitalizations can be due to cardiovascular or non-cardiovascular reasons, e.g., those for diagnostic procedures, elective interventions (like a device battery change), or planned operations. For a hospitalization to be considered unplanned, the patient must present with new symptoms (except accidents) and/or worsening of existing symptoms with the need for immediate admission into a hospital for intensified diagnostic tests and therapy (66).

*A normal 24h RR profile* for adults is defined as ≤ 135/≤ 85 mmHg (18) on average with at least 12h duration of 24h RR measurement and for children with blood pressure below the 95^th^ percentile. For patients without a valid 24h RR profile, their ambulatory blood pressure at month 12 will be imputed.

Good *eGFR* will be defined as eGFR ≥ 45 ml/min as determined by CKD-EPI (67) or Schwartz formula (68) at month 12. For patients without available eGFR at 12 months, their last available eGFR value will be carried forward.

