## Introduction

End-stage renal disease (ESRD) and kidney replacement therapies are linked to high morbidity and mortality (1). Compared to dialysis, kidney transplantation (KTx) offers the best survival, quality of life (QoL), and lower healthcare costs for patients with ESRD. According to current guidelines for immunosuppressive therapy, tacrolimus (a calcineurin inhibitor) combined with anti-IL-2 receptor antibodies (e.g., basiliximab), mycophenolate (e.g., Mycophenolate mofetil (MMF) or Enteric coated Mycophenolate sodium (EC-MPS)), and steroids, has significantly improved renal transplantation outcomes, particularly in reducing acute rejection rates to below 15% (2–5). As rejection is most common in the first year, early prevention is crucial for optimal outcomes, as rejections are linked to graft loss, prolonged hospitalizations, and over-immunosuppression. In addition, over-immunosuppression can increase infection risks, such as urinary tract infections (UTI), BK virus (BKV), and cytomegalovirus (CMV) (6–13). Thus, an adequate initial rejection prophylaxis is the key to optimal long-term outcomes in KTx.

Immunosuppressive drugs can also elevate cardiovascular risks, such as hypertension and diabetes, necessitating personalized treatment (14–19). The leading cause of graft loss remains death with a functioning graft, followed by T-cell mediated rejection (TCMR) and chronic antibody-mediated rejection (ABMR), often linked to non-adherence (20). Holistic care addressing adherence and cardiovascular risks through structured aftercare, adherence training, and sports therapy has been shown to improve graft survival (8, 21). This holistic approach, which systematically addresses non-adherence and cardiovascular risks in a structured aftercare program with adherence training and sports therapy, can lead to an improvement in graft survival, as demonstrated in our recent publication (22).

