### Recommendation on the indication and timing of graft biopsies

The indication for kidney transplant biopsies is at the discretion of the investigator. Unless a biopsy is medically contraindicated, it is strongly recommended to perform a kidney biopsy under the following circumstances: any unexplained rise in creatinine ≥25% compared to baseline in absence of an obvious clinical cause for rising creatinine (e.g., ureteral obstruction, renal artery stenosis, dehydration, urosepsis, polyoma virus infection, or drug toxicity); in any case of clinical suspicion for rejection with/without an unexplained decrease in urinary output, fever, and graft tenderness; as soon as possible after starting treatment for suspected rejection; at development or worsening of proteinuria.

*Surveillance biopsies* are at the discretion of the investigator(s) and will be read locally. All data from protocol biopsies will be collected within the eCRF. Results of pre-transplant biopsies will be captured in the eCRF.

All biopsies should be read locally and classified according to the most recent Banff classification. In addition, biopsies may be read in a central laboratory at a later stage and documented within the eCRF. In the case of any BPAR, it is strongly recommended to perform local HLA antibody testing.

*Graft failure* is defined as the initiation of chronic dialysis for a period of more than 30 days, allograft nephrectomy, listing for re-transplantation, or death with a functioning graft following randomization. Graft survival will be calculated from the date of randomization to the date of graft failure.

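### Unqualified carry-forward of eGFR credits patients who died or lost the graft with good month-12 renal function, and the IPV exemption for graft loss has no stated score

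*Protocol article*

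**What the plan says.** Under Study endpoints, the primary endpoint is an unweighted sum from 0 to 7: "Each indicator of the primary endpoint can be defined as achieved (=1) or not achieved (=0) for each patient". Three rules in that section matter here.

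- **eGFR** (at least 45 ml/min at month 12): "For patients without available eGFR at 12 months, their last available eGFR value will be carried forward". No group of patients is excepted.
- **Tacrolimus IPV** (below 30%): it "will be determined from tacrolimus trough levels at months 6, 7.5, 9, 10.5, and 12". Patients with levels of less than 3 are treated as failures, "except for patients with graft loss or switch to another immunosuppressant), high tacrolimus IPV will be assumed". The score of an exempted patient is not given.
- **BAASIS adherence**: "Patients who did not respond to the questionnaire at months 9 and 12 will be considered non-adherent". Here a missing result defaults to failure.

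Graft failure, a secondary endpoint, is defined at the end of the section on indication and timing of graft biopsies. The definition includes chronic dialysis for more than 30 days, allograft nephrectomy, "listing for re-transplantation, or death with a functioning graft following randomization". The separate Graft loss section gives a narrower definition that does not include death.

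**The concern.** The eGFR rule applies by its terms to anyone without a month-12 value, including patients who have died and patients on dialysis with no recorded eGFR. Such a patient can count as having good renal function at month 12 in the primary endpoint and as a graft failure in the secondary one. The case is not remote, since the Introduction says: "The leading cause of graft loss remains death with a functioning graft".

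The IPV rule does mention graft loss, but only to remove a penalty. Because every indicator must be 0 or 1, an analyst has to choose a score that the text does not supply, and could choose achieved.

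The Discussion presents the score as a measure of stable kidney function and good health. Points awarded after death or graft loss work against that reading, and they raise the mean of whichever arm has more such events.

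**Working it through.** The plan gives no figure on this point to reproduce. Its d = 0.31 serves only as a yardstick.

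**Step 1: apply the stated rules to an example.** Take a patient who dies with a functioning graft at month 4, with a last eGFR of 52 and no unplanned admission. I assume that no unplanned stay counts as achieved on both hospitalization indicators.

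| Indicator | Score | Reason |
|---|---|---|
| eGFR | 1 | 52 carried forward, and 52 ≥ 45 |
| BAASIS | 0 | no response at month 9 or 12 |
| IPV | 0 | sampling starts at month 6; death is not exempted |
| Unplanned hospitalizations | 1 | none occurred |
| Unplanned stays over 10 nights | 1 | none occurred |
| 24h blood pressure | open | the only fallback is a month-12 reading |
| De novo DSA | open | no month-12 test and no stated rule |

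The firm total is 3. Only the eGFR point comes from the carry-forward.

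**Step 2: graft loss.** If a month-12 eGFR below 45 is recorded, the indicator fails. The carry-forward matters only when that value is missing and the last one was 45 or more. The inclusion criterion (eGFR above 30 ml/min) allows this. Reading less than 3 as the number of levels, a patient with too few levels after graft loss is exempt from the assumed failure, and the IPV score is open. The two rules therefore affect one point for a death and at most two for a graft loss.

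**Step 3: size.** Assumed inputs, none given in the document: 12-month death or graft loss in 3% of one arm and 6% of the other; score SD 1.3; every such patient credited with the points in question.

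Shift in points = difference in event rates × points per event. Divide by the SD for SD units, then by 0.31 for the share of the planned effect.

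- eGFR point only: 0.03 × 1 = 0.03 points; 0.03 / 1.3 = 0.023 SD; 0.023 / 0.31 = 7%.
- eGFR and IPV points: 0.03 × 2 = 0.06 points; 0.06 / 1.3 = 0.046 SD; 0.046 / 0.31 = 15%. This is an upper case, because it treats every event as a graft loss with both points credited.
- Equal event rates: 0 × 1 or 2 = 0. The contrast does not move, although both arm means are slightly too high.

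**Step 4: range.** Let the difference in event rates run from 1 to 5 percentage points and the SD from 1.0 to 1.5. The eGFR point alone is then worth between 0.01 / (0.31 × 1.5) = 2% and 0.05 / (0.31 × 1.0) = 16% of the planned effect. With two points per event these figures double, to 4% and 32%.

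**The case against.** The strongest objection is that this is a condensed article. The full protocol and the SAP are not shown and may state how death and graft loss are scored. That stands against any complaint that a general rule is missing, and none is made here. It does not remove the point, because the carry-forward is a stated rule without qualification. An SAP rule that overrode it would have to be reconciled with this text.

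Three further objections stand. The carry-forward will seldom apply after graft loss. Graft failure, including death, is reported separately as a secondary endpoint. If the intervention reduces events, the bias works against it.

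Some stronger readings are tempting but not supported:

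- *The IPV exemption awards success, or covers death.* It only lifts an assumed failure, and death is not named. If less than 3 means a concentration rather than a count, the IPV part of this point lapses and the eGFR part remains.
- *An early death earns 4 to 5 of 7 points and scores near or above the average living patient.* The stated rules give 3 firm points; more would need blood pressure or DSA rules that the text does not contain. If indicator success rates are assumed to be spread evenly from 0.5 to 0.95, the mean is 7 × 0.725 = 5.1. A death at month 10 can reach 5, but apart from the eGFR point and the absence of admissions this rests on data recorded at months 6 to 9.
- *The distortion is 22–37% of the planned effect.* That charges all 3 to 5 points such a patient might collect to these rules (0.09–0.15 points, or 0.07–0.12 SD at SD 1.3). The rules account for one or two.

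**Conclusion.** The point holds in a limited form. The carry-forward, as written, credits month-12 renal function to patients whom the protocol elsewhere counts as graft failures. The IPV rule leaves graft-loss patients without the 0 or 1 that the endpoint requires.

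The effect on the treatment contrast is small: about 0.02 SD (7% of d = 0.31) for the eGFR point and at most about 0.05 SD (15%) with the IPV point. Both figures rest on assumed event rates of 3% versus 6%, an assumed SD of 1.3, and the credit going to every patient with an event. The shift favours the arm with more events and disappears at equal rates. The case for correction is that a stated rule in the primary endpoint gives a wrong result and is cheap to repair, not that it threatens the trial's conclusion.

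**What to change.** Make three changes to the endpoint definition or the SAP:

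1. Limit the eGFR carry-forward to patients alive with a functioning graft at month 12.
2. Score the eGFR indicator as not achieved after graft failure. Name the definition that includes death with a functioning graft, because the Graft loss section defines a different event.
3. State that graft-loss patients exempted from the IPV default score 0 on that indicator, and that less than 3 refers to the number of levels, if that is meant.

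Patients who switch immunosuppressant should not be left as missing on IPV, because the sum needs 0 or 1 from every patient.

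The change takes a few sentences and no new data, and a few patients will score slightly lower. Trial status gives 30 April 2026 as the expected last patient out. The wording should be settled and dated before database lock and before results by arm are seen, since a later change would look data-driven.
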